### Care and randomisation of patients

The standard care for breast cancer patients at each site is the same: following the cancer diagnosis, the medical files of the patients are examined at a multidisciplinary coordination meeting the purpose of which is to decide on the course of treatment to be given. Within a timescale of 1 to 2 weeks from the diagnosis, the patients are seen by an oncologist who explains to them what their course of medical treatment will consist of and whether or not this will involve chemotherapy. An appointment is then made for the following week with a nurse for a pre-chemotherapy consultation. During this interview lasting approximately 90 minutes, the nurse reviews with the patient what she has understood about the diagnosis and the treatment and her concerns and needs. The nurse can direct the patient to other professionals (psychologist, dietician, physiotherapist, welfare worker). The first chemotherapy session takes place approximately 1 month after this consultation.

The study is therefore proposed by the medical oncologist during the first care consultation to the patients fulfilling the inclusion criteria in the 2 investigating centres. After having explained the study to the patients with the information leaflet, those who accept sign a consent form. Next the patients will be randomised into two groups: 1) Group A: the « intervention » group which will have the benefit of the early active individualised psychosocial support in addition to the usual care. 2) Group B: the «standard care » group hereafter referred to as the “control group” which will follow the regular course of treatment without having the benefit of the psychosocial support as described above. This standard care already includes tools for identifying situations of great social distress enabling the patients to be directed to the regular social helpers.

Just after the inclusion, and before the start of their chemotherapy treatment, both groups of patients undergo the same battery of tests (pre-test).

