They are then invited to do the same battery of tests and fill in the questionnaires again by letter 12 months after the start of their chemotherapy treatment. Follow-up of the return to work in terms of the rate and the conditions and a follow-up of the quality of life are also done at 18 and 24 months. In the event of their failure to reply to the questionnaires, the patients are re-contacted twice by telephone within the space of 15 days following the sending out of the questionnaires (Figure 1).

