### Sample size

The number of patients was defined according to the expected reduction in the social inequalities of the return-to-work rate.

The research done by Quinton-Fantoni *et al. *[9] showed that the return-to-work rate 12 months after the diagnosis of women having had chemotherapy was 50% on average, but there was a difference of 22% between the most precarious and the least precarious cases.

The recruitment of 125 patients per group (A « intervention » and B « control »), with the acceptance of a first order risk of 5% and a power of 80%, would enable a reduction in the gap between the precarious cases and the non-precarious cases of 13.5 points to be demonstrated, enabling the difference in the return-to-work rate to be lowered from 22% to 8.5%. In order to make allowance for possible drop-outs during the study and unusable data, the minimum number of patients to be recruited was increased by 20%. The final number therefore comes to 150 women per group, i.e. a total of 300 patients.

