### Results expected

This is a multi-disciplinary project through which we hope the APAPI will enable a reduction in the social inequalities of the return to work (timescale, conditions, job retention rate) of the breast cancer patients compared with those who do not have the benefit of the APAPI.

The main observation we expect to make is that the social inequalities of the return-to-work rate 12 months after the diagnosis of the breast cancer patients are less for the APAPI group than for the control group.

We also expect to observe that this reduction in the inequalities in the intervention group compared with the control group also concerns the conditions and the return to work at 12, 18 and 24 months after the diagnosis, the psycho-social factors studied and worked on with the patients, that quality of life of the patients at 12, 18 and 24 months and the proportion of people having made use of the SEIS platform.

Another result expected is the overall improvement in all these factors in the intervention group compared with the control group.

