### Statistical analyses

The data will be entered twice then exploited in SAS V9.2 and SPSS v20. After the quality of the data has been checked and any corrections made, a description of the population included in the study will be given. A comparison of the main return-to-work criteria of the two groups drawn at random will be done (age, stage of development of the disease, occupational category).

The reduction in the social inequalities of the return to work will be studied by comparing the deltas (difference in the return-to-work rates between the two sub-groups FS + and FS-) between the control group « B » and the intervention group« A » having the benefit of the APAPI. A rough comparison of the two deltas will be done with a Chi2 test. The taking into account of adjustment factors (age, secondary effects of the treatment …) will be done with the aid of multivariate regression models.

As regards the secondary objectives, what is involved here is comparing for the 2 groups:

1) the deltas of the quality of the return to work at 18 and 24 months after the diagnosis (WAI and job retention rate); 2) the deltas of the psychosocial characteristics (QSSP, WCC, QAP, HADS and FACT-G scores) and the external resources (number of contacts with the SEIS platform) at 12 months from the diagnosis.

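### FACT-G is followed to 24 months and an effect is expected there, but its listed analysis stops at 12 months, and no score comparison names the pre-test

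*Protocol article*

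**What the plan says.** All the text is in the protocol article, Methods/Design.

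- **Collection.** Care and randomisation of patients says that "both groups of patients undergo the same battery of tests (pre-test") just after inclusion and before chemotherapy starts. The battery is repeated at 12 months. For later times the section names return to work (rate and conditions), and says that "a follow-up of the quality of life are also done at 18 and 24 months". Questionnaires and psychological tests names FACT-G as the quality-of-life instrument.
- **Expectation.** Results expected extends the predicted reduction in inequality to "that quality of life of the patients at 12, 18 and 24 months", and likewise to return to work and its conditions.
- **Analysis.** Statistical analyses has two secondary items. The first compares the Work Ability Index (WAI) and the job retention rate at 18 and 24 months. The second covers "the deltas of the psychosocial characteristics (QSSP, WCC, QAP, HADS and FACT-G scores") together with external resources ("number of contacts with the SEIS platform) at 12 months from the diagnosis"). FACT-G appears only in the second item.
- **Meaning of delta.** For return-to-work rates, the section defines a delta as the difference between the more and the less socially fragile women (FS+ and FS-), split at the median Epices score. It is not a change from baseline.

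**The concern.** The article does not leave the FACT-G time point open. It fixes 12 months, and this disagrees with its own data collection and its own expected results. If the plan is followed literally, the prediction for quality of life at 18 and 24 months is never tested. If it is not followed literally, the choice between 12 months alone and all three times would be made after the data are seen, which invites selective reporting.

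The second issue is precision. Each score contrast compares four cells (arm by fragility group), which is a noisy comparison at this sample size. The trial already measures every score before treatment on the same scale, and that value could remove part of the between-patient variation. The analysis text does not mention it.

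**Working it through.** **1. Time points side by side**

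| Outcome | Stated collection after the pre-test | Stated expectation | Listed analysis |
|---|---|---|---|
| FACT-G | 12, 18, 24 months | 12, 18, 24 months | 12 months only |
| QSSP, WCC, QAP, HADS | 12 months | no specific time given | 12 months |
| Return to work, later times | rate and conditions at 18, 24 months | 18, 24 months | WAI and job retention rate at 18, 24 months |

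Only the FACT-G row has a gap. In the last row the open question is whether the job retention rate is the same variable as the return-to-work rate. The term is not defined and could also be read as applying only to women who have already returned.

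**2. The plan's own sample size**

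Sample size gives "The recruitment of 125 patients per group" "with the acceptance of a first order risk of 5% and a power of 80" per cent, "enabling the difference in the return-to-work rate to be lowered from 22% to 8.5" per cent. Treating 0.22 and 0.085 as two simple proportions (two-sided 5%, 80% power):

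- Mean proportion 0.1525, difference 0.135.
- n = [1.96 × √(2 × 0.1525 × 0.8475) + 0.842 × √(0.22 × 0.78 + 0.085 × 0.915)]² / 0.135² = about 110.1, so 111 without continuity correction.
- With continuity correction: (110.1/4) × [1 + √(1 + 4/(110.1 × 0.135))]² = about 124.5, so 125. This matches the plan.
- 125 × 1.2 = 150 per group, which also matches.

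This figure sizes the primary outcome. No secondary score is sized, so 125 is used below only as the number analysed per arm. Whether a gap in rates may be treated as a simple proportion is a separate matter.

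**3. Precision of a score contrast**

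Inputs: 125 per arm; median split, so about 125/2 = 62.5 per cell; score SD set to 1; two-sided 5% and 80% power, so the multiplier is 1.960 + 0.842 = 2.802. Two-sidedness is an assumption, consistent with the match in step 2. The pre-test to follow-up correlation ρ is also assumed; the article gives none.

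- Follow-up score alone: SE = √(4/62.5) = 0.253 SD. Detectable contrast = 2.802 × 0.253 = 0.71 SD.
- With the pre-test as covariate: SE = 0.253 × √(1 − ρ²).

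| ρ (assumed) | Fall in variance (ρ²) | SE (SD) | Detectable contrast (SD) | Equivalent increase in n, 1/(1 − ρ²) |
|---|---|---|---|---|
| none used | – | 0.253 | 0.71 | 1.00 |
| 0.3 | 9% | 0.241 | 0.68 | 1.10 |
| 0.5 | 25% | 0.219 | 0.61 | 1.33 |
| 0.7 | 49% | 0.181 | 0.51 | 1.96 |

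**4. Is the pre-test usable as a covariate?**

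In Care and randomisation of patients, randomisation is described before the pre-test, and the pre-test comes before chemotherapy. Meetings with the psychologist places the first interview on the day of the first chemotherapy session. The pre-test therefore precedes any intervention contact. Women may, however, already know their allocation when they complete it, and that could colour self-reported scores.

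**The case against.** The strongest reply is that this is a journal article. Covariate choice for secondary scores normally sits in the full protocol or analysis plan, the adjustment list in Statistical analyses is open-ended, and nothing says that the pre-test is excluded. This stands: silence on baseline adjustment is not an error, and that part of the point is an improvement, not a defect. The pre-test also has other uses, since its results feed the second interview and the Epices score belongs to the questionnaire. In addition, the definition of delta is given for return-to-work rates, so carrying it over to the scores is a natural reading but still an inference.

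It can also be said that the secondary objectives in Intervention assessment methods tie 18 and 24 months to the quality of the return to work and give no time for quality of life, which agrees with Statistical analyses. That narrows the conflict but does not remove it, because the later quality-of-life data are collected and an effect on them is expressly predicted.

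A reader might infer more than the article supports:

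- **That all secondary scores are analysed at 12 months only.** WAI is compared at 18 and 24 months. For QSSP, WCC, QAP and HADS no collection after 12 months is stated, so no later data are ignored.
- **That the later return-to-work data go unused.** The job retention rate is compared at both times, and Results expected lists it as one aspect of return to work. What remains is an unclear term.
- **That the precision gain is large.** It depends on a correlation that the article does not give. A pre-test taken soon after diagnosis may correlate only weakly with the 12-month score, and at 0.3 the gain is small.

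**Conclusion.** The point holds in a limited form. The firm part is an internal mismatch on one secondary endpoint: FACT-G at 18 and 24 months is collected and predicted to show an effect, but has no listed analysis. This rests on the text alone and needs no assumption.

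The softer part is that the five 12-month score comparisons name no use of an identical pre-test. Using it would cut the variance of the contrast by 9% to 49% over assumed correlations of 0.3 to 0.7. This takes 125 analysed per arm, an even median split and two-sided testing. The true gain cannot be fixed from the article.

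The primary analysis is untouched. The change is worth making, but the trial's main conclusion does not depend on it.

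**What to change.** In Statistical analyses:

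1. Add the FACT-G comparisons at 18 and 24 months to the secondary list. One repeated-measures model over 12, 18 and 24 months is an option, but separate analyses at each time are enough.
2. Analyse QSSP, WCC, QAP, HADS and FACT-G by regression of the follow-up score on arm, Epices group, their interaction, centre and the pre-test score. The interaction is the contrast of interest. Centre belongs in the model because the Discussion says randomisation is done separately at each site.
3. State whether the job retention rate at 18 and 24 months is the return-to-work rate. If it is not, define it and its denominator, and list the return-to-work rate as well.
4. Bring the time points in Intervention assessment methods, Results expected and Statistical analyses into agreement.
5. Record that the pre-test follows randomisation and that patients may know their allocation when they complete it.

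The cost is wording, settled before the outcome data are examined. No new measurement, visit or patient is needed.

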### Medico-economic analyses

From the standpoint of the cost-benefit analysis, the APAPI support action protocol will be useful to implement compared with the conventional support action if the additional benefits are greater than the additional costs.

The point of departure for the analysis is situated in the identification of the mean marginal effect (in the population treated) of the support action on the probability of regaining employment after a certain fixed period of time (or over the time actually required itself). This effect is measured by the statistical model and provides the weighting for the various costs and benefits linked to this action.

The social security schemes and the company employing the person are the main beneficiaries of the early return to work through the number of days of sick leave saved and the rise in productivity due to the return to work of a person *in theory* better qualified than her replacement. On the markets where there is unemployment, the benefit will have to be reduced by the amount of the unemployment benefit paid to the replacement.

The monetary costs result mainly from the additional expenses incurred by the APAPI measure. They include the intervention of the psychologists and the investigating teams; it is then a question of calculating the net additional cost. It is however necessary to take into account the opportunity costs of the staff used for the intervention as they would be employed in other tasks if they were not involved in the APAPI measure. The monetary costs also include the fixed operating costs (facilities, equipment, expenses, etc.) and the cost of the increase in the activity of the SEIS platform.

*Ultimately*, several scenarios will be envisaged depending upon the elements that it is decided to include in the costs and benefits: various situations will be tested out to give a broad range of possibilities for the public decision-makers when making their assessment of the APAPI measure.

## Discussion

The originality of our study resides in the specific nature of our intervention. In point of fact, few interventions aim to reduce the social inequalities of the return to work of breast cancer patients.

Consistently with the previous research [3,27] our protocol is included in the existing course of treatment as early as possible so as not to make the patient support too unwieldy. The meetings with the psychologist therefore take place where the standard care is administered. Next, the inclusion of the SEIS platform enables interactive and personalised support to be offered to the participants that is directly linked to their work-related questions, which is different from most of the studies which supply an educational leaflet [13,33]. Lastly, in our intervention, the meetings are conducted by psychologists trained in cognitive behavioural therapies, enabling the psychosocial skills of the participants to be developed that relate to the problem solving techniques.

At the methods level, the purpose of our study is to develop an intervention that is assessed in the context of a randomised controlled trial, which constitutes the first strong point of our research. We have in fact taken into account the recommendations resulting from the previous studies deemed sometimes as weak from the methods standpoint, in particular because of the absence of a control group. The second strong point of the study resides in the participation of two of the region’s investigating centres in order to increase the heterogeneousness of the population studied. In point of fact each investigating site uses different socio-demographic and economic criteria for the investigation of its population. The Centre Oscar Lambret, located in the heart of the Lille metropolitan area, deals rather with patients from the tertiary sector, whereas the Centre Léonard de Vinci in Douai, which is located rather in an industrial and rural area, deals with the patients from primary and secondary sectors. Randomisation is therefore done independently at each investigating site in order to best preserve the socio-demographic criteria that will enable the social inequalities of the return to work to be observed.

The third strong point concerns the recruitment of the participants. In order to limit the biases, we chose to select women aged between 18 and 55 years; in point of fact beyond the age of 55 the French social security system proposes specific care packages enabling patients close to the retiring age not to return to work. In the light of the results of the literature on the impact of chemotherapy on the return-to-work time [11], we also opted to exclude any patient not given adjuvant chemotherapy.

In theory our study is likely to be inherently limited by the very construction of the protocol. In point of fact, given that the two investigating sites are located in the same region, there is a limit on the generalising of the results of the efficacy of this protocol at the national and even international level. What is more, APAPI is based on the SEIS platform which is not a standardised service in France. Thus the setting in place as it is of this intervention in other regions would require alternatives in terms of interactive individualised support equivalent to the SEIS platform. Moreover, in the light of the statistics, Nord-Pas-de-Calais is one of the regions in France most affected by cancer and unemployment. So, if the intervention successfully impacts the social inequalities of the return to work in our region, we consider we are justified in thinking that a similar scheme to APAPI would also act on these inequalities in other regions, provided the planned organisation is kept to: conducting of the interviews with the psychologist not requiring any additional travel on the part of the patients, conducting of the interviews with the physician specialising in job retention at the site where the patients are treated, communication by letter between the physician specialising in job retention, the GP and the occupational physician.

### Clinical prospects

The data collated from the A « intervention » and B « control » groups will enable the difficulties and socio-professional inequalities usually encountered by breast cancer patients to be identified, as well as the medical, social, psychological and economic determinants.

The identification of the psycho-socio-economic determinants as return-to-work factors would enable optimisation of the support for breast cancer patients. The generalising of support practices on the basis of the relevant factors holds out the prospect of a positive economic impact and above all better return-to-work conditions for the people having been treated for cancer with the aim of maintaining an acceptable quality of life for them, creating a dynamic and positive repercussions on everything that may have been affected by the cancer and its treatment (sphere of social, professional and personal life, psycho-social skills).

The aim of this support being to take into account and modify certain factors of psychosocial fragility (poor perceived social support, little in the way of developed coping strategies, attitude to negative problems), we expect to observe a benefit for all the patients but a greater one for those in a situation of social fragility.

We hope to test out an original intervention that offers, not the same thing for everyone, but more for those who are in greater need than the others, so as to reduce the dual and even triple distress when the sick person is in a situation of social, psychological and/or occupational fragility.

## Abbreviations

APAPI: Early active individualised psychosocial support; EPICES: Evaluation de la précarité et des inégalités de santé pour les centres d’examens de santé; GP: General practioner; SEIS: Health-employment-information-services; CHRU: University hospital centre; QSSP: Questionnaire de soutien social perçu; WCC: Ways of coping check list; QAP: Questionnaire d’attitude face aux problèmes; HADS: Hospital anxiety and depression scale; FACT-G: Functionnal assessment of cancer therapy - General; WAI: Work ability index.
